## Abstract

**Background:** In-time treatment of acute stroke is critical to saving people’s lives and improving the quality of post-stroke life. A mobile stroke unit (MSU) with fifth-generation (5G) mobile networks strengthens the interaction of patient information and healthcare resources, thereby reducing response times and improving thrombolysis results. However, clinical evidence of better outcomes compared to regular care is still lacking.

**Method and Design:** In this randomized controlled trial, 484 patients with acute stroke are allocated into the MSU and regular care groups. We establish medical records for each patient and conduct a follow-up of 90 days. The primary outcomes are functional results as defined by utility-weighted modified Rankin Scale (uw-mRS) 90 days after the incidence occurred, whereas secondary outcomes include the alarm to CT scan completed time, the alarm to treatment decision time, the alarm to thrombolytic time, quality of life, and symptomatic intracranial hemorrhage combined with NIHSS score as well as cost-effectiveness.

**Discussion:** This study establishes an innovative MSU (based on 5G) to manage acute stroke, comparing its clinical and economic outcomes to regular care and informing decision-makers of the effectiveness of the stroke emergency system.

**Clinical Trial Registration:** [http://www.chictr.org.cn/showproj.aspx?proj=63874], identifier [ChiCTR2000039695].

## Introduction

Patients with acute stroke require medical aid at the first moment to quickly work out suitable treatment options, thus minimizing adverse results after stroke (Peisker et al., 2017). Clinical guidelines propose that prehospital treatment, including ambulance arrangement and tissue plasminogen activator (t-PA) treatment, is essential to saving patients with acute stroke and improving their quality of life (Powers et al., 2018, 2019). To this end, an emergency medical system (EMS) with a quick response to stroke calling and well-trained emergency personnel is needed. Emergency experts have been searching for innovative approaches that transcend the conventional pathway to provide patients with better medical services. A mobile stroke unit (MSU) is a special ambulance that incorporates neurological examination, CT diagnosis, and intravenous thrombolytic therapy by fitting a mobile CT and relevant point-of-care laboratory testing (Bowry and Grotta, 2017; Tsivgoulis et al., 2018).

As a timely administration of thrombolytic therapy, MSU has apparent benefits for acute stroke patients (Nyberg et al., 2018; Yamal et al., 2018). In China, the MSU equipped with a mobile CT was introduced in 2017, effectively reducing the “door to needle” from over 60 min to around 48 min. As a result, hospitals have established their MSUs across the country, in efforts to elevate the local medical services and social welfare (Zhou et al., 2021). Moreover, with the recent universalization of fifth-generation (5G) technology, the MSU has gradually transformed into a new model by equipping with the latest mobile networks and state-of-the-art monitoring devices, balancing essential functions of EMS and other advanced gadgets. Therefore, the highly informative and intelligent MSU enables rapid treatment of acute stroke, reducing stroke patients’ disability and death rates and the economic burden on their family as well as the entire society. Furthermore, the highly integrated wearable devices could acquire the core medical data (including vital signs, cranial pressure monitoring, blood glucose, etc.) in real time, which is simultaneously uploaded to a stroke-specific cloud platform for remote consultation and better surveillance.

## Methods and Analysis

### Study Design

We conduct a pragmatic, prospective trial to examine clinical and economic outcomes in patients eligible for thrombolytic administration who receive care from MSU, as compared with regular care in a blinded fashion (see Figure 1), determining. Through this, we aim to determine whether the deployment of MSU leads to better functional benefits for patients with acute stroke. Investigators randomly allocate one patient to either the MSU or the regular care group. To balance the two groups on potential confounding factors (such as weather) that may change in a year, we choose a block size of 4 weeks to limit the length of time to use the same program.

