### Participants

A total of 484 participants are recruited from the Ya’an people’s Hospital, 242 of whom were randomized to the intervention group and the rest randomized to the comparison group.

Each participant must meet all of the inclusion criteria to be enrolled in this study, which are given as follows:

1.Patients need to be aged over 18 years, with a final diagnosis of ischemic stroke.2.Patients’ confirmed onset-to-alarm time is less than 4.5 h.3.Patient is recognized as a t-PA candidate, with mRS scores less than 3.4.Patients volunteer to participate and sign an informed consent.

The exclusion criteria include uncertain symptom onset, no focal stroke-like symptoms, severe malignant, or pregnancy.

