### Intervention and Comparison

The case group is treated in the MSU, which is designed to establish a treatment unit integrating neurological symptom examination and CT diagnosis, achieving intravenous thrombolytic therapy and remote consultation at the first moment. During transportation, the physician can carry out neurological evaluation (NIHSS scores), blood glucose, coagulation index detection, and head CT scanning on the ambulance where data are transmitted to the stroke center in real time through 5G networks for technical support and treatment guidance from experts. Once the patient is recognized as suitable for thrombolysis, t-PA treatment will be given within the “golden time” of stroke management. The MSU team includes a paramedic, a stroke doctor, and a neuroradiologist, integrating the conventional EMS in a mixed urban–rural environment. The patient is evaluated for vital signs and neurological impairment followed by head CT screening and blood biochemical examination. The patients who meet the requirements of intravenous thrombolysis will be given t-PA treatment on the MSU vehicle after the informed consent is signed. Those who are not suitable for intravenous thrombolysis will be transported to the stroke center for further treatment. If necessary, remote consultation will be carried out through a customized telemedicine system based on 5G technologies. The MSU adopts a 7-day 24-h working system. In contrast, the control group is treated through conventional EMS in which the city emergency medical rescue center dispatches an ordinary ambulance. Head CT screening, blood biochemical examination, and the followed t-PA treatment (if suitable) will be performed after patients are delivered to the hospital’s emergency center (Nor et al., 2005) (see Figure 2).

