### Statistical Analysis

We calculate the sample size by comparing two independent samples. A *t*-test compares the mean uw-mRS at 90 days and corresponding two-sided 95% confidence intervals if the assumption of normality is not valid. Although the mRS is a primary endpoint, the difference among the uw-mRS categories is significant, and the *t*-test assumption and central limit theorem are probably met. The calculation of uw-mRS will be adjusted for baseline uw-mRS and baseline covariates associated with mRS in a linear regression model. Stratified analyses of the primary outcome and pooled measures are conducted by the Cochran–Mantel–Haenszel analyses and multiple ordinal regressions. We use a proportional odds model to process dichotomized outcomes of uw-mRS 0-1 vs. 2-6 with binary logistic regression. Participants in the intervention group who give up during the program will be excluded from the analysis. In addition, subjects in both treatment groups will be excluded from the protocol analysis if any violations of the following protocols after randomization and during intervention and follow-up. All analyses are performed by SPSS 27.0.

Besides, we explore the missing data and compare the distribution of critical variables. Suppose there is a reasonable amount of missing data and the data summary indicates that the data are missing at random. In that case, all analyses will be performed after multiple imputations of missing data using baseline variables as auxiliary variables.

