## Discussion

This study explores whether stroke patients clinically benefit from MSU deployment at 90 days. Given that many countries have encountered problems resulting from the increasing elderly population and related burden of cerebrovascular diseases, this finding could project some hope on emergency care based on the latest mobile networks and state-of-the-art devices to relieve stroke-related problems. As an expensive and complicated intervention, prehospital stroke management presents different models globally, making its clinical outcomes and cost-effectiveness difficult to evaluate, thus limiting its widespread utilization. Although some famous research works about the MSU gain better results about the clinical application (Kunz et al., 2016; Ebinger et al., 2021), the evidence is insufficient due to the limited sample size, unstandardized disposition of devices, and economic conditions of varied regions in the world. Therefore, a prospective controlled trial based on China’s experience can provide healthcare decision-makers with clinical and administrative data in developing countries. However, selection bias by distributing patients according to MSU availability is hardly avoided, potentially causing the baseline information to be divided in the end. Second, the accurate data of uw-mRS are hardly accessed through telephone interviews. Therefore, we try to eliminate the offset by conducting multi-dimensional follow-ups through the Wechat survey applet. Third, a potential challenge is that it is difficult to identify patients with suspected stroke to suitable distribution in the dispatch center after an emergency call was made, thus making the prehospital stroke management unaccessible. Limited availability weakens a clear comparison group with all critical factors of a prospective study where MSU is compared to regular care. Overall, potential bias will be minimized by operationalized standards and adjustment for baseline parameters.

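### Study Design and Discussion give conflicting accounts of allocation (random per patient, an ambiguous 4-week time block, MSU availability), and the validity of the analysis depends on which one holds

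*Protocol article*

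**What the plan says.** Four parts of the protocol article bear on allocation.

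- **Study Design** makes the patient the unit: "Investigators randomly allocate one patient to either the MSU or the regular care group". To balance factors that vary over the year, such as weather, it then says: "we choose a block size of 4 weeks to limit the length of time to use the same program".
- **Participants** agrees with randomisation, describing 484 patients, "242 of whom were randomized to the intervention group and the rest randomized to the comparison group". The Abstract also calls the study a randomised controlled trial.
- **Intervention and Comparison** says of the unit's hours: "The MSU adopts a 7-day 24-h working system".
- **Discussion**, among the limitations, says that "selection bias by distributing patients according to MSU availability is hardly avoided". It adds that limited availability weakens the comparison group, and it relies on operational standards and baseline adjustment to reduce bias.

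The **Statistical Analysis** section treats patients as independent. On sample size it says "We calculate the sample size by comparing two independent samples". The primary test "compares the mean uw-mRS at 90 days and corresponding two-sided 95% confidence intervals", and a further model is "adjusted for baseline uw-mRS and baseline covariates associated with mRS in a linear regression model". It names no time block or period, but it also does not list its covariates.

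**The concern.** Random allocation and assignment by availability cannot both describe how a patient reached an arm. Whether an MSU is free plausibly depends on concurrent calls, distance and time of day. Each of these could also be related to outcome, and the article names none of them as an adjustment variable. If availability decides the arm, the causal claim loses the protection of randomisation, and a regression on measured baselines does not restore it.

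The 4-week block raises a second, separate question. A block measured in weeks, whose purpose is to limit how long one programme runs, can be read as giving a stretch of calendar time to one arm. Patients in that stretch would share arm, season and staffing, so a patient-level test would treat correlated outcomes as independent. Availability is therefore a problem of bias, and period allocation is a problem of the standard error. Both turn on a fact that the article leaves open.

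**Working it through.** **1. The accounts side by side**

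| Reading | Source | Random? | Is the patient-level t-test valid? |
|---|---|---|---|
| Each patient randomised | Study Design, first statement; Participants; Abstract | Yes | Yes |
| Patients randomised within 4-week blocks | Study Design, block sentence, one reading | Yes | Yes; omitting the block can only cost precision |
| Whole periods allocated to one arm | Study Design, block sentence, other reading | Yes, if periods are randomised | No, if outcomes correlate within periods |
| MSU availability decides | Discussion | No | The main fault is confounding, not the standard error |

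The first two rows are compatible with each other. The last is compatible with none of the others.

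**2. The plan's own figure**

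Inputs from Sample Size Estimation: difference 0.09, SD 0.5, two-sided alpha 0.05, power 0.80, 10% dropout, 484 in total.

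n per arm = 2 × [0.5 × (1.960 + 0.842) / 0.09]² = 484.5, so 485 per arm, 970 in total, and 970/0.9 = 1,078 with dropout.

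The stated total of 484 is therefore not reproduced; it matches the per-arm number before dropout. That is a separate matter, but it sets the baseline here. With 218 per arm (242 less 10%) and independent patients, power at a difference of 0.09 is 46.8%.

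**3. If whole periods are allocated to one arm**

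The article gives no recruitment length, period length or intraclass correlation (ICC). Assumed: recruitment over 1 to 2 years, weekly or 4-weekly single-arm periods of equal size, ICC 0.01 to 0.05.

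- Patients per period: m = 484/104 = 4.7 and 484/52 = 9.3 (weekly); 484/26 = 18.6 and 484/13 = 37.2 (4-weekly).
- Design effect: DE = 1 + (m − 1) × ICC.
- Actual type I error of the t-test: 2 × [1 − Φ(1.96/√DE)].

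| m | ICC | DE | True SE ÷ t-test SE | Type I error |
|---|---|---|---|---|
| 5 | 0.01 | 1.04 | 1.02 | 5.5% |
| 5 | 0.05 | 1.20 | 1.10 | 7.4% |
| 18.6 | 0.01 | 1.18 | 1.08 | 7.1% |
| 18.6 | 0.05 | 1.88 | 1.37 | 15.3% |
| 37.2 | 0.01 | 1.36 | 1.17 | 9.3% |
| 37.2 | 0.05 | 2.81 | 1.68 | 24.2% |

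With a correctly sized test, the 46.8% power above becomes that of 218/DE patients per arm: about 45% in the first row and about 20% in the last.

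**4. If availability decides**

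The article gives nothing from which to compute a bias. As an illustration only: if 10% to 20% of the regular-care arm were there because the MSU was not free, and their mean uw-mRS differed by 0.1 to 0.2 for reasons unrelated to treatment, the shift would be 0.10 × 0.1 = 0.01 to 0.20 × 0.2 = 0.04, against a target difference of 0.09. Its direction is unknown.

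**The case against.** Four objections have force.

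- **The analysis is not at odds with every description.** A reader might infer that it fits none of the accounts and that the standard errors are simply wrong. The documents do not support this. An independent-samples t-test is the standard match for per-patient randomisation, which is the first account given. The standard error is too small only if whole periods are allocated and outcomes correlate within them.
- **The block sentence is ambiguous.** Its stated aim is balance between groups, which fits randomising individuals within time blocks. The phrase about using the same programme leans towards calendar periods but does not settle it.
- **The availability sentence is in a limitations paragraph.** It may mean that availability sometimes disturbed an intended random assignment, which would be non-adherence. Round-the-clock operation does not contradict it, since a unit on duty day and night can still be occupied. But the sentence speaks of distributing patients by availability and names selection bias as the result, so it has to be reconciled with Study Design.
- **A block or period term may be in the full protocol or SAP.** An article need not list its covariates, so the missing term is not itself an error. The contradiction about allocation is in the published text and is not a matter of omitted detail.

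The numerical ranges also rest wholly on assumed inputs. The 24% figure needs the longest periods, the shortest recruitment and the highest ICC together.

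**Conclusion.** The concern holds in a limited form. The article's accounts of allocation conflict, and a reader cannot tell from them whether this is an individually randomised trial, a trial that allocates periods, or a non-randomised comparison.

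The contradiction between random allocation and assignment by availability rests on the text alone. The standard-error problem is conditional on period allocation: under the assumptions shown, a design effect of about 1.04 to 2.8 and a type I error of about 5.5% to 24%. Under individual randomisation, with or without time blocks, there is no inflation. The size of any availability bias cannot be determined from the article.

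This should be resolved before the analysis is fixed, because both the label of the trial and the correct model depend on it.

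**What to change.** 1. **State one unit and one mechanism** in Study Design and make the Discussion agree. Set the arm from a pre-generated, concealed schedule and not by availability.
2. **Analyse every enrolled patient in the assigned arm**, including when the MSU was scheduled but not available.
3. **Put the 4-week block in the primary regression** where both arms occur within a block. If a 4-week period is itself the single-arm unit, a fixed block term is confounded with arm and step 4 applies instead.
4. **If periods are the unit**, use period-level cluster-robust standard errors or a period random effect, and restate the power with the assumed ICC and period size. With as few as 13 to 26 periods (the 4-weekly case above), a small-sample correction is needed.
5. **Keep the availability limitation**, reworded as non-adherence to the assigned arm. Deleting it would only hide a disclosed weakness. If availability did decide the arm, describe the trial as non-randomised throughout, including the Abstract.

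The cost is a protocol amendment and a few model terms if practice already follows a random schedule, and a change in trial conduct if it does not. Analysing as assigned slightly dilutes the effect when the MSU could not attend. Under period allocation the confidence interval is wider and the stated power lower.

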**FIGURE 1 F1:**
[figure not shown]
Flow diagram of patients screening. **(A)** Conventional emergency medical system. **(B)** 5G-based mobile stroke unit.

The protocol that is registered with No. ChiCTR2000039695 on 5 November 2020 (http://www.chictr.org.cn/showproj.aspx?proj=63874) has been approved by the ethical review committee of the Ya’an people’s Hospital (NPSY202007002).

### Participants

A total of 484 participants are recruited from the Ya’an people’s Hospital, 242 of whom were randomized to the intervention group and the rest randomized to the comparison group.

Each participant must meet all of the inclusion criteria to be enrolled in this study, which are given as follows:

1.Patients need to be aged over 18 years, with a final diagnosis of ischemic stroke.2.Patients’ confirmed onset-to-alarm time is less than 4.5 h.3.Patient is recognized as a t-PA candidate, with mRS scores less than 3.4.Patients volunteer to participate and sign an informed consent.

The exclusion criteria include uncertain symptom onset, no focal stroke-like symptoms, severe malignant, or pregnancy.

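### The entry criteria do not require a stroke suspected at the call within MSU reach, so regular care, but not the MSU arm, can include patients with no chance of the MSU

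*Protocol article*

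**What the plan says.** The Participants section presents its list as the condition of entry: "Each participant must meet all of the inclusion criteria to be enrolled in this study". It names four criteria:

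- age and diagnosis: "Patients need to be aged over 18 years, with a final diagnosis of ischemic stroke";
- timing: "confirmed onset-to-alarm time is less than 4.5 h";
- t-PA candidacy with an mRS score below 3;
- informed consent.

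On exclusions it says: "The exclusion criteria include uncertain symptom onset, no focal stroke-like symptoms, severe malignant, or pregnancy". On recruitment it says: "A total of 484 participants are recruited from the Ya’an people’s Hospital".

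For regular care, Intervention and Comparison says that "the city emergency medical rescue center dispatches an ordinary ambulance", and that CT, blood tests and any t-PA follow once the patient is in hospital. The same section describes the setting as mixed urban and rural and gives no MSU service area.

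Study Design says that investigators randomly allocate each patient and sets a block of 4 weeks. It does not say at what moment a patient is allocated.

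The Discussion names recognition by the dispatcher as a possible obstacle: "difficult to identify patients with suspected stroke to suitable distribution in the dispatch center after an emergency call was made". It spells out no frequency, but it does name the result for the patients concerned: "thus making the prehospital stroke management unaccessible". It also concedes that selection arises because patients are assigned by whether the MSU is available. Its answer is operational standards and adjustment for baseline.

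**The concern.** A fair comparison of two dispatch options needs every participant to have been able to receive either one at the moment the choice was made. For an MSU patient this holds automatically, because the vehicle was sent. For a regular-care patient the written criteria do not secure it. A stroke not recognised at the call, or a call from an address the MSU could not serve, goes by ordinary ambulance. If it is recognised in hospital, it can meet every listed criterion there.

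Two things are at stake. The arms may differ in case mix, which can shift the 90-day uw-mRS difference. The three alarm-based time endpoints may also differ because a stroke was recognised late or the address was remote, rather than because of the vehicle.

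Baseline adjustment can remove imbalance that runs through measured covariates. It cannot restore comparability for patients whose defining feature, no chance of the MSU, has no counterpart in the MSU arm.

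**Working it through.** The article gives no figure on this point. The check is a reading of each criterion, followed by an illustration of size.

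**Step 1. Each entry condition against the two missing ones.**

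| Condition (Participants) | What it fixes | Stroke suspected at call? | Address in MSU reach? |
|---|---|---|---|
| Adult, final diagnosis of ischemic stroke | Known after work-up | Not required | Not required |
| Onset-to-alarm under 4.5 h | That an alarm was raised, and when | Not required | Not required |
| t-PA candidate, mRS below 3 | Candidacy settled after assessment; in regular care, in hospital | Not required | Not required |
| Consent | Willingness | Not required | Not required |
| Exclusions | The patient's condition, not the dispatcher's judgement | Not required | Not required |

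**Step 2. Trace two patients.** Both have focal symptoms and call within 4.5 h.

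- Patient A is recognised as a suspected stroke at an address the MSU serves. A could be sent either vehicle and could be in either arm.
- Patient B is not recognised at the call, or is out of reach. B can only travel by ordinary ambulance, is diagnosed in hospital and meets the same list. If B is enrolled, it is as regular care.

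**Step 3. What would close the gap.** Randomisation at dispatch, restricted to suspected and reachable calls, would keep B out of both arms. Study Design does not place randomisation there. Hospital recruitment, eligibility by final diagnosis, a block measured in weeks and the conceded role of MSU availability all point away from it.

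**Step 4. Illustration of size.** Let f be the share of regular-care patients with no chance of the MSU, and d their mean uw-mRS minus that of the other controls. If the other controls are comparable with the MSU arm:

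bias in (MSU - regular care) = -f × d

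Inputs from Sample Size Estimation: planned difference 0.59 - 0.50 = 0.09, SD 0.5, 242 per group. Assumed, not in the article: f = 0.10 to 0.30 and d = 0.05 to 0.10 in either direction.

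SE of the difference = 0.5 × √(2/242) = 0.0455. With no true effect, the two-sided rejection rate is Φ(-1.96 + b/SE) + Φ(-1.96 - b/SE), where b is the size of the bias.

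| f | size of d | size of bias | share of 0.09 | rejection rate under no effect |
|---|---|---|---|---|
| 0.10 | 0.05 | 0.005 | 6% | 0.0514 |
| 0.10 | 0.10 | 0.010 | 11% | 0.0556 |
| 0.20 | 0.05 | 0.010 | 11% | 0.0556 |
| 0.20 | 0.10 | 0.020 | 22% | 0.0725 |
| 0.30 | 0.05 | 0.015 | 17% | 0.0626 |
| 0.30 | 0.10 | 0.030 | 33% | 0.1012 |

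Last row: 0.30 × 0.10 = 0.03, and 0.03/0.0455 = 0.66, so Φ(-1.30) + Φ(-2.62) = 0.0968 + 0.0044 = 0.1012.

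The 242 per group is taken as stated. It does not follow from the stated inputs (the two-sided formula gives 485 per group before dropout), but that is a separate matter and this point does not depend on it.

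**The case against.** The strongest reply is that this is a consequence of how patients are allocated. The article calls the trial randomised. If that happens among suspected strokes at the call, missed strokes cannot enter one arm only. Figure 1, the screening diagram, is not shown and may contain a dispatch step, and a full protocol may say more. This stands as a limit: the finding concerns what the written criteria allow and does not show that such patients are enrolled. It does not dispose of the point, because the text presents the list as the conditions of entry, does not state when allocation occurs, and itself concedes both the dispatch problem and the role of availability.

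The exclusion of patients without focal symptoms and the t-PA requirement also trim atypical or late-recognised strokes. That is fair and may make the affected share small, but neither criterion refers to recognition at the call or to location.

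Three stronger readings are tempting and are not supported:

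- A reader might infer that dispatch frequently misses stroke. The Discussion calls this difficult and a potential challenge, and gives no frequency.
- A reader might infer that the bias favours the MSU. Nothing in the article says whether unrecognised or remote strokes fare worse or better than the others.
- A reader might measure a time bias against the fall from over 60 to around 48 min in the Introduction. That is a door-to-needle interval from earlier MSU use in China. It is neither an alarm-based interval nor an effect planned for this trial.

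**Conclusion.** The point holds as a gap in the entry criteria. As written, they let regular care, but not the MSU arm, take in strokes that had no chance of the MSU, unless randomisation occurs at dispatch among suspected, reachable calls. The article does not state that condition, and its remarks on availability sit badly with it.

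The primary comparison can be biased in an unknown direction, and the alarm-based times can be distorted. Neither size can be computed from the article. The range of 0.005 to 0.03, at most one third of the planned 0.09, rests wholly on the assumed shares and differences. Confidence is moderate, because Figure 1 and the full protocol are not shown. The criteria should be amended, since the stated remedy of baseline adjustment does not reach the problem.

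**What to change.** Add one criterion, applied identically in both arms and verified from dispatch records: stroke was suspected at the emergency call and the address lay inside a defined MSU service area. Fix eligibility and allocation at that point, regardless of whether the MSU is then free, and analyse everyone who meets the criterion as allocated. Without this last part, a dispatch code alone would leave selection by availability in place.

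List strokes not recognised at dispatch, or outside the area, separately and in neither arm. Limit the conclusion to strokes recognised at the call. If allocation already works this way, stating it in Study Design and Participants is enough.

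The cost is one criterion, a written service area and a check of dispatch records, with somewhat slower accrual and a narrower target population than a pragmatic trial might want. The article does not say whether the dispatch centre records a suspected-stroke code. If it does not, that field would have to be introduced.

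### Enrolment depends on a final diagnosis and t-PA candidacy that appear to be settled after the arm is set, and at a different time and place in each arm, so the compared groups may be selected differently

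*Protocol article*

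**What the plan says.** Participants (protocol article) states that "Each participant must meet all of the inclusion criteria to be enrolled in this study". Among those criteria are "Patients need to be aged over 18 years, with a final diagnosis of ischemic stroke", recognition as a t-PA candidate with an mRS below 3, and written consent. The only time limit is that "onset-to-alarm time is less than 4.5 h".

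Study Design states that "Investigators randomly allocate one patient to either the MSU or the regular care group", and adds that "we choose a block size of 4 weeks to limit the length of time to use the same program". It does not say at what moment a patient is allocated.

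Intervention and Comparison describes the work-up by arm. In the MSU, "During transportation, the physician can carry out neurological evaluation (NIHSS scores), blood glucose, coagulation index detection, and head CT scanning on the ambulance". Of the patients carried there, "Those who are not suitable for intravenous thrombolysis will be transported to the stroke center for further treatment". In regular care an ordinary ambulance is sent, and head CT, blood tests and "the followed t-PA treatment (if suitable) will be performed after patients are delivered" to the hospital's emergency center.

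The Discussion admits selection bias from sharing out patients by whether an MSU is available, and says that suspected stroke is hard to identify at the dispatch center after the call. It relies on operational standards and baseline adjustment to limit bias.

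**The concern.** Randomization protects a comparison when membership of the analysed groups is fixed by facts that the arm cannot influence. Age and onset-to-alarm time are such facts. A final diagnosis and a judgment of t-PA candidacy are not, if they are reached after the vehicle has been chosen and by a different team, in a different place and at a different interval from the alarm. Two patients with the same onset, the same alarm time and the same illness could then be counted in one arm and left out of the other.

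The primary result would then mix the effect of the MSU with a difference in who was counted. The planned adjustment for baseline covariates in a linear regression cannot reliably undo this, because the selection happens after allocation and may depend on the arm through features that the baseline data do not record.

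**Working it through.** The article gives no figure for differential selection, so there is none to reproduce. The check has two parts: the order of events, and an illustration of scale.

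**1. Order of events**

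| Step | MSU arm | Regular care | Source |
|---|---|---|---|
| Alarm; onset-to-alarm time fixed | same | same | Participants |
| Vehicle goes to the patient | MSU | ordinary ambulance | Intervention and Comparison |
| CT and laboratory tests | on the vehicle, with remote expert support | in the hospital emergency center | Intervention and Comparison |
| t-PA suitability judged | on the vehicle | after delivery to hospital | Intervention and Comparison |
| Final diagnosis | after the work-up | after the work-up | Participants; follows from the rows above |

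- The vehicle is what distinguishes the arms, and the work-up takes place in or after it. If allocation decides the vehicle, it must come before the work-up and so before both late criteria.
- The same order follows if the 4-week block means that a calendar program sets the arm: the arm is then known even earlier.
- The Discussion fits this order, since it treats the sharing-out of patients as a dispatch matter.
- The time criterion stops at the alarm. It fixes entry on the time scale but does not equalise the moment at which candidacy is judged.

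Participants admits only recognised t-PA candidates, while Intervention and Comparison provides for MSU patients found unsuitable and makes control t-PA conditional on suitability. The article does not say whether the unsuitable patients belong to the trial.

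**2. Scale, with assumed inputs**

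From Sample Size Estimation: planned difference 0.59 − 0.50 = 0.09, SD 0.5, 242 per arm. Assumed, not in the article: a share *f* of one arm's counted patients would not have been counted in the other, and their mean uw-mRS differs by *d* from the rest.

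With no true effect and mean μ for the rest, one arm has mean (1 − f)μ + f(μ + d) = μ + f·d and the other has μ. The bias is f·d.

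Standard error = 0.5 × √(2/242) = 0.0455. The two-sided type I error at nominal 5% is P(Z > 1.96 − b) + P(Z < −1.96 − b), with b = f·d / 0.0455.

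| f | d | Bias f·d | Share of 0.09 | Type I error |
|---|---|---|---|---|
| 5% | 0.1 | 0.005 | 6% | 5.1% |
| 10% | 0.2 | 0.02 | 22% | 7.2% |
| 20% | 0.3 | 0.06 | 67% | 26.2% |

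The bottom row needs both assumptions at their extreme.

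**The case against.** The strongest reply is that the order of events is inferred. Study Design does not say when allocation happens, and the screening flow diagram, which might show it, is not available here. This stands, and the point is conditional on it. The inference is firmest for the final diagnosis, which needs the work-up that takes place in or after the vehicle.

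Second, t-PA-eligible ischemic stroke is a legitimate target population, and blinded adjudication of eligibility could be in the full protocol. This also stands. The point is not that a procedure is missing, but that the article makes these late facts conditions of enrolment. Its statement that the comparison is blinded does not say who makes the diagnosis or whether that person knows the arm, and the team on the vehicle necessarily knows it.

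Third, the authors acknowledge selection bias and plan adjustment. The acknowledgement is fair; the adjustment does not cure selection after allocation.

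A reader might infer more than the article supports:

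- *That the groups are in fact selected differently.* The article shows a route by which this can happen, not that it does.
- *That both arms demonstrably contain enrolled patients unsuitable for t-PA, so that two sections contradict each other.* Intervention and Comparison says what happens to patients who are carried. They may be carried without being enrolled. The text is unclear rather than necessarily contradictory.
- *That candidacy expires with delay after the alarm.* The only stated limit is onset to alarm, and whether candidacy carries a later one is undefined. The point does not need such a limit: a different place, team and moment of assessment suffice.
- *That early recovery after treatment can remove a patient's final diagnosis.* Nothing in the article says so, and it is not relied on here.

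**Conclusion.** The concern holds as a design risk. As written, enrolment depends on two facts that appear to be established after the arm is set and under different conditions in each arm, so the arm may influence who is counted.

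Neither the size nor the direction of the bias can be computed from the article. The range of 0.005 to 0.06 shows only what the assumed inputs imply; in the middle case the distortion of type I error is modest, from 5% to about 7%. The conclusion rests on reading the vehicle as the allocated intervention. It would fall away for any criterion shown to be settled before allocation, or judged by a rule that the arm cannot affect.

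**What to change.** 1. State when allocation occurs relative to each inclusion criterion, including consent.
2. Reconcile Participants with Intervention and Comparison on whether patients found unsuitable for t-PA are in the trial and in the primary comparison.
3. Keep t-PA-eligible ischemic stroke as the primary target population, but define membership of that analysis set by one written rule applied identically in both arms. The rule should use onset and alarm times and information not affected by delay after the alarm, and should be applied from records without arm identity where feasible. It governs the analysis set only and is not a treatment criterion.
4. Pre-specify a sensitivity analysis of all allocated patients who consent and meet the criteria fixed before allocation: age, onset-to-alarm time, mRS (read here as the score before the stroke) and focal stroke-like symptoms.
5. Report by arm the numbers allocated, not consenting, and excluded at each step.

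The cost is protocol wording, one added analysis and 90-day calls to some further patients, whose number the article does not allow to be estimated. The effect in the sensitivity analysis will be diluted by non-ischemic and unsuitable cases, which is why it is not proposed as the primary analysis. Symptoms at the call are also an imperfect criterion, since the Discussion says that suspected stroke is hard to recognise at dispatch.

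One source of selection remains. In the MSU arm a signature is described on the vehicle before t-PA. If that is also consent to the trial, it is given once the arm is known, and these changes make its effect visible without removing it.
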